### Study setting

We will recruit participants from two public primary schools in the Western Cape province of South Africa and in collaboration with a non-governmental organisation (NGO). The NGO operates onsite within schools in the Western Cape to improve the social and emotional well-being of children and promote supportive school communities. The two schools were randomly chosen (using computer randomisation) from a list of schools (*N* = 21) within which the NGO operates. Both schools have a staff to learner ratio of approximately 40:1, and both schools form part of South Africa’s National School Nutrition Programme [42]. Schools are eligible for funding for this nutrition programme when most of the children come from low socio-economic status families. In total, each school has approximately 30–34 teachers and 900–1000 pupils.

### Characteristics of participants

Participants will be in grade 5 at participating schools (aged ~ 10–13 years). The intervention will be universally delivered, i.e. delivered to all participating children regardless of symptomatology or risk. Given the restrictions posed on this research by COVID-19 and given changes to school scheduling, we pragmatically decided to target the intervention at one grade, grade 5, only. There are approximately 20 eligible children per class with 6 and 8 classes at our target schools respectively. As such, whilst there are approximately 280 children eligible to take part in grade 5 across these 2 schools, we expect a sample of approximately 224 children to take part in this study which accounts for a 20% non-participation rate. We will calculate consent and retention rates at immediate post-intervention as well as 1-month follow-up. As per communication received from the Western Cape Education Department (WCED), no research may be conducted during the fourth term (October–December 2021) as schools are preparing and finalising syllabi for examinations. This could then mean that a 1-month follow-up assessment might not be possible with the children in the DIG.

### Ethical review and consent

Ethical approval has been obtained from Stellenbosch University’s Research Ethics Committee: Social Behavioural and Education Research (project number: 9183), and reciprocity has been received from the Psychology Research Ethics Committee (reference number: 19-073) at the University of Bath. The WCED approved of the study being conducted in the two schools (reference: 20200214-4483).

All grade 5 children in both schools will be informed about the intervention and will be given a project information sheet to take home. The information sheet will include an opt-out consent form to be returned if parents/caregivers do not wish their child to be part of the intervention. In addition, children will also be asked to complete assent forms prior to completing baseline assessments. Children whose parents do not agree to participate or who themselves do not provide assent will be supervised in a separate classroom. Children will not be required to provide reasons for not taking part. Once consent and assent have been received, post-graduate psychology students will administer the baseline battery of measures to children one class at a time. The programme facilitators will be on standby should children require individual assistance with the completion of the measures.

### Procedures

Assessments will be completed at baseline, post-intervention, and at 1-month follow-up. Measures will be completed in school, over two or three lessons. Researchers with a post-graduate degree in Psychology will read assessment items out loud as children individually respond to each question in their assessment booklet. Participants will have the option to complete forms in either English or Afrikaans. We will provide children with a thank you gift in the form of a 4STMF wrist band after completion of the intervention sessions, and the completed assessment battery.

The language of the programme delivery will be in the predominant language of each class, either English or Afrikaans. Programme facilitators will be trained to deliver the programme fluently in both languages. Class teachers will be encouraged to attend the lessons delivered and may be involved in disciplinary processes if necessary, during the lessons, but will not be expected to deliver the programme material.

Following completion of the 4 Steps To My Future (8 lessons) programme, children will complete the assessment battery, and again at a 1-month follow-up. On completion of intervention delivery, a subgroup of participants stratified to include both male and female participants will be invited to take part in focus group discussions to share their experiences of the programme.

### Outcome measures

All participants will provide demographic information at baseline (see Fig. 1). The schedule of data collection is shown in Fig. 3.

**Fig. 3 Fig3:**
[figure not shown]
Overview of the project timeline. IIG immediate intervention group, DIG delayed intervention group

### Feasibility

To determine whether it is feasible to deliver the intervention and assessment measures, we will collect the following feasibility and acceptability outcomes:Rates of parental opt-out: How many parents/caregivers refused consent for their child to take part in the programme? For this outcome, we will count the number of consent forms returned from parents. As mentioned, we will use parental opt-out. As such, parents who sign and return the consent form will do so indicating that they do not want their child to take part in the study.Rates of child assent: How many children declined to take part in the programme? For this outcome, we will count the number of assent forms handed out and then the number of forms returned by learners invited at baseline. We will provide each child in grade 5 with an assent form. We will subtract the number handed out from the number of forms returned.Rates of assessment completion: How many participating children completed assessments at baseline, post-intervention, and 1-month follow-up? For this outcome, we will count the number of children who completed assessments at each time point. We will subtract the number of completed measures from the number who provided consent at baseline to determine how many assessments were not completed at each time point.Programme completion: How many groups received all 8 sessions of 4 Steps To My Future? For this outcome, observers will document session delivery to each group/class of learners. Observers will capture whether a session was delivered in full or not.Session attendance: How many children attended each session of the programme? For this outcome, we will count the number of learners present in class for each session delivery. We will then obtain class attendance records from the class teacher to document which learners (who consented to take part) were present or absent.Programme fidelity: How many programme sessions were delivered fully, as intended. For this outcome, observers will capture on observation templates whether a session was delivered fully as intended or not. The observer will be instructed to note what circumstances interfered with session delivery as intended.

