**Methods:**

This is a feasibility pilot study of 4 Steps To My Future (4STMF), a Cognitive Behaviour Therapy (CBT) school-based programme for young adolescents in the Western Cape, South Africa. This eight-session intervention will be delivered to children in grade 5 (aged 10–13 years approximately) attending two public government-run schools in the Western Cape, South Africa. We aim to enrol approximately 224 children in grade 5. We will randomise which school receives the intervention first and the other will be a delayed intervention group. We will train individuals with a post-graduate degree in psychology to facilitate the programme. We will collect demographic data on participants as well as data on primary (feasibility measures) and secondary outcomes (mental health and well-being measures). We will collect data at baseline, post-intervention, and at 1-month follow-up.

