### Feasibility trial objectives

The primary objective of this study is to determine the acceptability and feasibility of the 4STMF programme. We will use a mixed methods design utilising quantitative and qualitative methods. We will determine acceptability and feasibility through assessing consent and assent rates, as well as session and programme completion rates. Fidelity checklists will be completed by the programme facilitators and independent observers for each lesson. These fidelity checks will elicit how confident, prepared, and enthusiastic facilitators appeared whilst delivering the programme, as well as how well they managed the classroom. Furthermore, the fidelity checklists will elicit how long it took to deliver a lesson, whether an activity was delivered or changed, and how confident, prepared, and enthusiastic the facilitators appeared during the delivery of that lesson. Furthermore, teachers will be asked to complete an evaluation form once the programme has been facilitated. Qualitative, semi-structured exit focus groups will be conducted with CYP following intervention delivery. We will determine the acceptability of our assessment measures (completion rates) and will explore pre- and post-intervention changes to determine sample size (power) for a future randomised controlled trial (RCT).

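### The child assent outcome is calculated as forms returned minus forms handed out, which cannot be positive; with the order corrected it still counts unreturned forms, including those of children opted out by a parent, and not refusals.

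*Protocol article*

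**What the plan says.** The abstract of the protocol article classes the feasibility measures as the primary outcomes. The section on feasibility trial objectives adds: "We will determine acceptability and feasibility through assessing consent and assent rates, as well as session and programme completion rates".

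The Feasibility section defines the assent item in four steps.

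- The question: "Rates of child assent: How many children declined to take part in the programme".
- The counts: "we will count the number of assent forms handed out and then the number of forms returned by learners invited at baseline".
- Who receives a form: "We will provide each child in grade 5 with an assent form".
- The calculation: "We will subtract the number handed out from the number of forms returned".

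Parental opt-out is a separate outcome in the same list, counted from returned forms: "parents who sign and return the consent form will do so indicating that they do not want their child to take part in the study". The section on ethical review and consent describes how that form reaches parents: "The information sheet will include an opt-out consent form to be returned if parents/caregivers do not wish their child to be part of the intervention". It treats parental refusal and lack of child assent as two distinct reasons for not taking part.

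**The concern.** Returned minus handed out has the smaller number first, so it cannot answer a question about how many children declined. The next item in the list, assessment completion, subtracts from the larger number, so the reversal is a slip in this item and not a convention of the article.

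The sign is the lesser problem. Handed out minus returned equals the number who declined only if every unreturned form is a child's refusal. The rule for handing out forms makes no exception for children whose parents have opted out. Such a child has no reason to return an assent form, and would then appear under two outcomes that are meant to be distinct. The item is also headed as a rate, while its rule yields a difference of two counts.

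What is at stake is the use of the pilot. It is meant to inform a full trial, and parental opt-out and child refusal call for different responses when recruitment is planned. A rule that merges them, and counts some children twice, gives a participant flow that does not add up.

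**Working it through.** **Inputs.** The section on characteristics of participants gives about 20 eligible children per class, 6 and 8 classes in the two schools, about 280 eligible children, 20% non-participation and an expected sample of about 224. No split of the non-participants by reason is given.

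**1. Reproduce the plan's figures.** 20 × (6 + 8) = 280. 280 × (1 - 0.20) = 224. Both agree with the article.

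**2. Apply the rule as written.** Let H be forms handed out and R forms returned. Take H = 280, and R = 224 by assuming one returned form per participant and none from anyone else. Then R - H = 224 - 280 = -56.

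**3. Reverse the order.** H - R = 280 - 224 = 56, or 56/280 = 20.0% of the roll. This is simply all non-participants, whatever the reason.

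**4. Separate the reasons.** Let o be the children opted out by a parent and a the children not asked (for example, absent). Refusals are 56 - o - a, and children asked number 280 - o - a. The values of o and a are assumptions.

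| Opted out (o) | Not asked (a) | Refused | Asked | Refusal | Assent | Sign-corrected rule reports as declined |
|---|---|---|---|---|---|---|
| 0 | 0 | 56 | 280 | 20.0% | 80.0% | 56 |
| 28 | 0 | 28 | 252 | 11.1% | 88.9% | 56 |
| 28 | 14 | 14 | 238 | 5.9% | 94.1% | 56 |
| 56 | 0 | 0 | 224 | 0% | 100% | 56 |

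The last column never changes, so the rule cannot tell these situations apart. The third row also assumes that a form counts as handed out for a child who was not asked, which the article does not say. The other rows need only that opted-out children are given a form and do not return it.

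**5. The double count.** In the second row, the sign-corrected rule reports 56 child refusals and the opt-out outcome reports 28. Together that is 56 + 28 = 84 non-participants, when there are 280 - 224 = 56. The excess is exactly the number opted out.

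**6. Returned refusals.** If a form can be handed back marked as a refusal, it counts as returned. With 14 such forms, R = 224 + 14 = 238 and R - H = 238 - 280 = -42, so those 14 children drop out of the count of decliners. Whether the form allows this is not stated.

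**The case against.** The strongest reply is that the question shows what is meant. Handed out minus returned is the obvious intention, and nobody would publish a negative number of decliners. That is fair: taken alone, the sign is a wording slip that would be caught.

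It can also be said that the forms are returned by learners invited at baseline, which may leave opted-out children out. If they are not given forms, if absent children are not either, and if refusing means not returning the form, the sign-corrected rule gives exactly the number who declined. But the sentence that follows gives the form to every grade 5 child, so the text as it stands points the other way. Opt-outs are counted separately, so the overlap could be removed at reporting if they can be matched to the assent list. The written rule does not call for this.

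The missing denominator is minor, since both counts are collected and a proportion can be formed. What remains open is which children belong in it.

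A reader might go further and infer that the rule counts absent children as having declined and misses explicit refusals. The article supports neither as a fact. It does not mention absence here, and a child who was never handed a form leaves both counts. It does not say that an assent form can record a refusal; a returned form may simply mean assent.

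**Conclusion.** The definition is wrong as written and should be corrected. Two parts follow from the text: the subtraction is reversed (-56 on the expected numbers, with one returned form per participant), and giving a form to every grade 5 child allows children opted out by a parent to be counted as child refusals as well. The second part assumes that such children do not return the form. Depending on the split of the 56 expected non-participants, true refusal among children asked lies between 0% and 20%, and assent between 100% and 80%. That range shows what the rule cannot distinguish; it does not predict the error.

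It would be too strong to say that the reported figure will be badly wrong, or that it could not be used to plan the full trial. The outcome is descriptive, no test, sample size or stated progression threshold depends on it, and the expected overall participation of 224 out of 280 is unaffected. This is a point to fix, not one that undermines the study.

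**What to change.** Replace the calculation with: assent rate = children who give assent / children asked for assent whose parents did not opt out. Report parental opt-outs, child refusals and children not asked (such as those absent) as separate, non-overlapping counts which, with the children who assent, sum to the eligible grade 5 roll. State how an unreturned form from a child who was asked is classified, and whether the form can record a refusal.

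The cost is one reworded definition and one column on the class list for each child's status. The column is best filled in when assent is sought, because the reason for an unreturned form may not be recoverable later. If assent has already been taken, opt-outs can still be removed from the count where the returned parental forms can be matched to the class list, and the remaining unreturned forms should then be reported as such and not as refusals.

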### Intervention

The intervention will be delivered during the Life Orientation (LO) or Personal and Social Wellbeing (PSW) lessons, or at a time deemed most suitable by the respective school principals and teachers. The LO and PSW lessons are part of the South African national education curriculum and are aimed at providing children with basic skills and knowledge regarding health, society, rights and responsibilities, physical education, and preparation for the world of work.

Both the immediate intervention group as well as the delayed intervention group will receive the programme in a face-to-face whole class delivery format.

The intervention is informed by CBT and throughout the 8 sessions teaches skills in four main areas. Table 1 provides an overview of the components of the programme. Firstly, participants are encouraged to develop their self-esteem through identifying their personal strengths, accepting who they are, and being kind to themselves and others. The second introduces children to their cognitions and the importance of developing “go” thinking (positive, enabling, and balanced). Thirdly, children are encouraged to attend to how they feel and to positively manage strong unpleasant emotions. Finally, children are encouraged to identify their future goals, to break these down into steps, and to learn to problem solve to address issues that might impede their attainment.

**Table 1 Tab1:** Components of the 4STMF intervention package

Theoretical framework (intervention)	Cognitive behavioural therapy (CBT) based with a focus on psychoeducation, resilience, skills-building, and well-being
**Interventionists/delivery agents**	• Registered counsellors/masters-level psychology students with 1–2 years of research experience and who attended training on the intervention package; masters-level psychology students with 1–2 years of research experience who will act as observers and conduct fidelity checks
**Structure of intervention package**	• Eight × 20–25-min sessions, delivered over 4 to 8 weeks (delivered either weekly or twice weekly depending on fit with school)
**Structure of sessions**	• The programme is split into 4 steps — and each step contains 2 lessons. Participants in the immediate intervention group (IIG) and the delayed intervention group (DIG) receive the intervention
**Step 1 lesson 1**	• Introduction to 4STMF (5 min)
	• Self-esteem and respect (10 min)
	• Remember your strengths (6 min)

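### Which children attended each session is taken from the class teacher's record, which may not have been made at the session; an observer-ticked list would be a better source at almost no cost

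*Protocol article*

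**What the plan says.** The Feasibility section of the protocol article poses the outcome as a number: "Session attendance: How many children attended each session of the programme". It then names two sources.

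- **Number present.** The first source is a count made in the lesson: "we will count the number of learners present in class for each session delivery". No names are attached to it.
- **Which children.** The second source supplies identity: "We will then obtain class attendance records from the class teacher to document which learners (who consented to take part) were present or absent".

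Under Procedures, the teacher's presence is optional: "Class teachers will be encouraged to attend the lessons delivered and may be involved in disciplinary processes if necessary". Under Intervention, the lesson falls in a timetabled life-skills period or "at a time deemed most suitable by the respective school principals and teachers". Observers are in the lesson, but the task given to them under programme completion is a group-level one: "observers will document session delivery to each group/class of learners". Their other stated task is fidelity. A named roll is not among them.

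**The concern.** The only stated source that ties a child to a session is a record kept by someone who need not be in the room. A register taken once in the day shows that a child was at school. It does not show that the child sat through a particular 20–25 minute lesson.

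The article makes feasibility measures the primary outcomes. Its programme-completion outcome counts groups that received all eight sessions, not children. The attendance record is therefore the only stated measure of how much of the programme an individual child received. If it reflects presence at school, child-level exposure would tend to be overstated. Children who were at school but not in the lesson would also be hidden, and they are informative about acceptability.

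**Working it through.** **Step 1: reproduce the plan's denominator.** From Characteristics of participants: (6 + 8) classes × 20 eligible children = 280, and 280 × (1 − 0.20) = 224, as stated. That is 224 / 14 = 16 participants per class and 224 × 8 = 1,792 child-session records. No figure in the plan is in dispute.

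**Step 2: what each source can answer.** The head count is made at the session. Children without consent or assent are supervised elsewhere ("who themselves do not provide assent will be supervised in a separate classroom"), so the count should cover participants only. It answers the outcome as worded, but it cannot give sessions per child. Take a class of 16 with a head count of 15 at all eight sessions, which is 120 of 128 child-sessions. If the same child is missing every time, 15 of 16 children received the whole programme. If a different child is missing each time, only 8 of 16 did. Separating these cases needs names, and the article takes the names from the teacher's record.

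**Step 3: possible size of the error.** The documents give no attendance rates and do not say whether the teacher's record is daily or per lesson. The following assumes a daily register. Let *a* be the proportion at school and *m* the proportion of those who miss the session.

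- Register reads *a*; true attendance is *a*(1 − *m*); the gap per session is 224·*a*·*m* children.
- With independence across sessions, the share attending all eight is *a*⁸ by the register and [*a*(1 − *m*)]⁸ in truth.

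| *a* | *m* | Register | True | Gap (children per session) | All 8, register | All 8, true |
|---|---|---|---|---|---|---|
| 0.95 | 0 | 95% | 95.0% | 0 | 66% | 66% |
| 0.95 | 0.02 | 95% | 93.1% | 4.3 | 66% | 56% |
| 0.95 | 0.05 | 95% | 90.3% | 10.6 | 66% | 44% |
| 0.95 | 0.10 | 95% | 85.5% | 21.3 | 66% | 29% |
| 0.90 | 0 | 90% | 90.0% | 0 | 43% | 43% |
| 0.90 | 0.02 | 90% | 88.2% | 4.0 | 43% | 37% |
| 0.90 | 0.05 | 90% | 85.5% | 10.1 | 43% | 29% |
| 0.90 | 0.10 | 90% | 81.0% | 20.2 | 43% | 18.5% |

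The rows with *m* = 0 also describe a record taken at the session, where the error is zero. The head count would reveal the per-session gap but not which children made it up. The all-eight columns only show how a small error accumulates over sessions; that share is not an outcome the article lists.

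**The case against.** The strongest reply is that the two sources are complementary, one for number and one for identity, and that the outcome as worded is answered by the head count. That stands. A reader might infer that reported per-session attendance will be too high. The text does not support this, because it would require the head count to be set aside in favour of the teacher's record, and nothing says so.

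A reader might also infer that a child at school but out of the lesson definitely will be scored as attending. That does not follow either. The article speaks of class attendance records and does not call them a daily register. Delivery is to whole classes, so class and session may largely coincide, and a teacher who attends could take the record there.

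Two supporting arguments should not be used. The separate classroom is described for children without parental agreement or assent, not for those who withdraw later. Disciplinary involvement of teachers is described as happening during the lessons, so a teacher involved would know of a removal.

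Finally, how lists are kept and reconciled is the kind of detail a condensed article may leave to the full protocol. That lowers the weight of the point but does not dispose of it. The article is not silent on the child-level source. It assigns it to the class teacher, although people who are certain to be in the lesson could supply it.

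**Conclusion.** The point holds as a minor one. The stated source for which children were present need not reflect presence at the session, because the teacher who keeps it need not be there and no named roll in the lesson is described. The number attending each session is protected by the head count. What is exposed is child-level attendance: who missed, and sessions per child. These may be overstated and may disagree with the count.

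The size cannot be determined from the document. It is zero if the record is taken at the session. Under the assumed rates with a daily register, it runs from about 4 to about 21 children per session out of 224. No listed analysis is invalidated.

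**What to change.** Give the observer already in each lesson a pre-printed list of that class's participating children by study ID, to be ticked at every session. Check the ticks against the head count on the spot, and name this list as the source for child-level attendance. Keep the teacher's record for one purpose: to classify each absence as not at school, or at school but not in the session. The second category is useful acceptability evidence in its own right.

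The cost is one printed list per class (14 in all) and about a minute of observer time per lesson, with no extra staff.
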